8.2. PROVIDE A DETAILED ANALYSIS PLAN

Simple summary statistics will be calculated for each outcome and regression analysis used to control for predictive variables. Data will be tested for distribution and differences between groups using unpaired t-tests, Mann-Whitney U tests and Chi squared tests as appropriate, based on recruitment.

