**8. STATISTICAL CONSIDERATIONS**

8.1. SAMPLE SIZE OR POWER CALCULATION

Power Calculation - with n=1000 patients per group, the upper limit of the observed one-sided 95% confidence interval for the difference between failure rates (seed vs wire) is expected to be less than 0.9% with 80% power, assuming the two methods both have an expected failure rate of 0.6%. Hence, if a 0.9% difference is considered an acceptable equivalence margin (eg. 0.6% for wire and 1.5% for seed), 1000 patients per group should be sufficient to establish equivalence.

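### Section 8.2 does not carry forward the confidence limit on which 8.1 bases the Savi Scout versus wire margin claim, and the tests of difference it names cannot support that claim

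*Protocol*

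**What the plan says.** Protocol 8.1 (repeated in the synopsis under statistical considerations) justifies the sample size by a confidence limit set against a margin. The quantity it uses is "the upper limit of the observed one-sided 95% confidence interval for the difference between failure rates (seed vs wire"). Its claim is that this limit "is expected to be less than 0.9% with 80% power". Behind the claim stands a failure rate of 0.6% with either method. The margin itself is put conditionally: "if a 0.9% difference is considered an acceptable equivalence margin (eg. 0.6% for wire and 1.5% for seed"). From this the section concludes that "1000 patients per group should be sufficient to establish equivalence".

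Protocol 8.2, headed as the detailed analysis plan, has two sentences. The first reads "Simple summary statistics will be calculated for each outcome and regression analysis used to control for predictive variables". The second covers distributional checks and "differences between groups using unpaired t-tests, Mann-Whitney U tests and Chi squared tests as appropriate". Neither sentence names a confidence interval for a difference, the 0.9% margin, or a rule for concluding equivalence or non-inferiority. The synopsis puts the 8.1 and 8.2 texts in one cell without linking them.

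The comparison with hookwire is the secondary objective (3.2). Section 6.1 says that the same parameters will be compared in a wire cohort recruited from a single institution.

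**The concern.** The quantity that justified 1000 per group is an upper confidence limit below 0.9%. The analysis section names t, Mann-Whitney and chi-squared tests for two-group comparisons, and for a binary failure outcome that means chi-squared. The null hypothesis of that test is no difference. A non-significant result does not bound the difference below 0.9%, and a significant one does not show that 0.9% is exceeded.

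This is more than detail left for an analysis plan. Section 8.2 names a type of test that does not match the conclusion 8.1 is built on. An analyst who follows 8.2 has no margin analysis to report, and one who follows 8.1 goes beyond 8.2. With about 6 failures expected per group (1000 × 0.6%), non-significance is the likely result, so the way a p-value is read matters.

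**Working it through.** **Inputs.** From 8.1: 1000 per group, one-sided 95% limit, both failure rates 0.6%, margin 0.9 percentage points, and a device at the margin having 1.5% against 0.6% for wire. From 8.2: chi-squared as the two-group test for a binary outcome. Assumptions: a two-sided 5% level for that test (8.2 states none), 1000 wires as in 8.1 (6.1 gives no number), and no dropout.

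**1. The plan's own figure.** With unpooled variance, SE = √(2 × 0.006 × 0.994 / 1000) = 0.345%.
- The limit attainable with 80% power is (1.645 + 0.842) × 0.345% = 0.859%, which is below 0.9%.
- Power at 0.9% is Φ(0.900/0.345 − 1.645) = Φ(0.961) = 83.2%. Exact enumeration of two binomials with the Wald limit gives 83.5%.
- Solved for n, the same formula gives 911 per group.

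So 1000 per group is sufficient for the criterion as written.

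**2. Chi-squared at the margin (0.6% against 1.5%).** The pooled rate is 1.05%.
- Null SE = √(2 × 0.0105 × 0.9895 / 1000) = 0.456%, so the critical difference is 1.96 × 0.456% = 0.893%.
- Alternative SE = √((0.006 × 0.994 + 0.015 × 0.985) / 1000) = 0.455%.
- Power = Φ((0.900 − 0.893)/0.455) = 50.6%, so non-significance is 49.4% by normal approximation.

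**3. How often each rule would pass a device.**

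| Rule (1000 per group, exact unless noted) | At the margin (1.5% vs 0.6%) | Both at 0.6% |
|---|---|---|
| Chi-squared non-significant, two-sided 5% | 47.8% | 95.6% |
| Same, Yates correction | 58.8% | 97.7% |
| Fisher's exact test non-significant | 57.5% | 97.6% |
| One-sided 5% test non-significant, normal approximation | 37.1% | – |
| Upper one-sided 95% limit below 0.9%, Wald | 6.5% | 83.5% |
| Upper one-sided 95% limit below 0.9%, score (Farrington-Manning) | 4.8% | 77.6% |

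**4. Sensitivity to the wire cohort size** (assumed range, Savi Scout fixed at 1000). Chi-squared non-significance at the margin is 94.5% with 200 wires, 68.7% with 500 and 32.6% with 2000.

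**5. The rules disagree in both directions.**
- 12 Savi Scout failures against 6 wire failures: chi-squared = 2.02, p = 0.155. The Wald upper limit is 0.6% + 1.645 × √((0.012 × 0.988 + 0.006 × 0.994)/1000) = 0.6% + 1.645 × 0.422% = 1.29% (score 1.38%). There is no significant difference, and the margin is not met.
- 4 against 0: uncorrected chi-squared = 4.01, p = 0.045. The Wald upper limit is 0.4% + 1.645 × √(0.004 × 0.996/1000) = 0.73%. The difference is significant, and the margin is met.

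**The case against.** The strongest reply is that Section 8 should be read as a whole: 8.1 gives the criterion, and 8.2 lists general methods to be used as appropriate. The only equivalence criterion in the protocol is the 8.1 limit, which is described as an observed quantity and so would be computed from the study data. The failure counts from the summary statistics would be enough to compute it. Most of what 6.1 compares, such as specimen weight, timing, reoperation, cancellations and complications, has no margin, and difference tests are ordinary choices there. Regression is also named, so tests of difference are not the whole plan. The comparison is a secondary objective in an audit, and 8.1 words the margin conditionally.

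Much of this stands. A reader might infer that the protocol intends to declare equivalence from a non-significant chi-squared. No sentence says so, and the 48% is the error rate of that misreading, not of a stated rule. A reader might also infer that the 80% power is wrong. It is not: it holds for the limit as described and falls to about 78% only if a score limit is chosen.

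What the reply does not remove is that the section headed as the analysis plan omits the one analysis that justifies the sample size. It attaches no margin to the regression, and the two-group tests it does name cannot yield the conclusion in 8.1.

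**Conclusion.** The point holds in a limited form. Sections 8.1 and 8.2 are not joined: the upper limit that supports the margin claim is absent from the analysis plan, and the named tests of difference cannot replace it. If non-significance were taken as equivalence, a device exactly at the margin would pass about 48% of the time (59% with Yates, about 37% with a one-sided 5% test), against about 5% (score) to 6.5% (Wald) under the 8.1 limit. Those figures assume 1000 per group and, for the 48% and 59%, a two-sided 5% level that the protocol does not state. They move with the size of the wire cohort.

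The severity is moderate: the objective is secondary, although it is the only one with a sample-size calculation.

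**What to change.** In 8.2 and the synopsis:
- State that the conclusion on localisation failure rests only on the one-sided 95% upper confidence limit for the risk difference (Savi Scout minus wire) being below 0.9%. Because only an upper limit is used, the accurate word is non-inferiority rather than equivalence.
- Preferably name a score method (Miettinen-Nurminen or Farrington-Manning), because only about 6 failures per group are expected and the Wald limit passes a device at the margin 6.5% of the time instead of 5%.
- Report a regression-adjusted estimate alongside, because the wire cohort is non-randomised and comes from one institution.
- Keep the t, Mann-Whitney and chi-squared tests for outcomes without a margin, and say that their p-values do not support the margin claim.

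The cost is a few sentences, with no change to data collection or recruitment. The 80% power statement can stay for a Wald limit. If the score limit is adopted, note that power at 1000 per group is about 78%.

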5.4 CONFOUNDERS

5.5 STUDY LIMITATIONS

Given that this is a multi-centre study, there will be differences in the radiologist’s technique in placing the Savi Scout® localisation device and the surgeon’s technique in retrieving the targeted lesion.

This may mean that if a particular group has a large contribution to the dataset, the results may be skewed.

This study is a prospective audit and does not have the same level of evidence as a randomised controlled trial.

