**6. STUDY PROCEDURES**

6.1. INVESTIGATION PLAN

The multicentre component of the trial involves a prospective audit of information relating to the use of Savi Scout®.

This involves documenting this data into a secure web-based Redcap database.

The dataset collected is the same from every international site.

There is no intervention that is carried out for the study as this is an audit.

The procedures related to Savi Scout® placement are part of normal practice and are not influenced by this study given the collection of data occurs after the decision to use Savi Scout®. Savi Scout® is an established technology for localisation of impalpable breast lesions and axillary nodes at Chris O’Brien Lifehouse.

This audit will have data contributed from multiple sites globally. The information collected will investigate the margin status of excision, accuracy of placement, timing of the placement of Savi Scout®, and the proportion of Savi Scout® placed at the time of biopsy, pathological weight of specimen, size of MRI bloom around Savi Scout® , transcutaneous detection rate, reoperation rate, complications, cancellation rate on day of surgery, reason for cancellation on day of surgery, time of day of start of surgery and identification rate of axillary nodes using Savi Scout.

Comparative analysis will be performed with the same parameters for participants that have undergone hookwire-localisation of impalpable breast lesions. Information of the hookwire-localisation cohort have been recruited from Manchester University NHS Foundation Trust/Manchester University.

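### The group comparisons named in section 8.2 assume independent patients, although the protocol expects technique to differ between centres, so precision is probably overstated by an amount it does not let us fix

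*Protocol*

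**What the plan says.** Section 8.2 describes the comparison of groups as "using unpaired t-tests, Mann-Whitney U tests and Chi squared tests", with the choice among them left to depend on recruitment. The sentence before it also plans summary statistics and "regression analysis used to control for predictive variables", without naming the covariates, a site term or a variance estimator.

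Section 5.5 says that because the study is multi-centre, "there will be differences in the radiologist’s technique in placing the Savi Scout® localisation device and the surgeon’s technique" in retrieving the lesion. It adds that "if a particular group has a large contribution to the dataset, the results may be skewed". The heading for section 5.4, on confounders, has no text under it.

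On data sources, section 6.1 says "This audit will have data contributed from multiple sites globally", whereas for the comparator "Information of the hookwire-localisation cohort have been recruited from Manchester University NHS Foundation Trust/Manchester University".

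Section 8.1 bases its power statement on 1000 patients per group, a failure rate of 0.6% in both groups, a margin of 0.9 percentage points and a one-sided 95% limit. It mentions no allowance for clustering.

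**The concern.** The t-test, the Mann-Whitney test and the chi-squared test all take each patient as a separate piece of information. If outcomes depend on who places the reflector and who operates, patients at one centre resemble each other and 1000 Savi Scout patients carry less information than 1000 independent ones. The protocol says that it expects this dependence and then names tests that exclude it. So this is a stated method at odds with a stated expectation, and more than a detail left for later.

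The asymmetry of the two cohorts matters. Had each site supplied both methods, part of the site effect would cancel in the difference. Here it cannot, because the Savi Scout patients are spread over sites and the wire patients are not.

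At stake are the unadjusted p-values and standard errors for every pooled Savi Scout outcome, and the error rate and power of the 0.9-point comparison in 8.1.

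**Working it through.** **Inputs from the protocol.** 1000 per group, 0.6% failure in both groups, 0.9-point margin with the example 1.5% against 0.6%, one-sided 95% limit, 80% power (8.1). Expected number at the Australian site: 50 (4.2). Pooled Savi Scout re-excision rate from the cited systematic review: 12.8% (1.1).

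**Assumptions.** The protocol gives neither an ICC nor a number of sites. I take ICC from 0.001 to 0.05 and 50 patients per site, the only site size stated, which means 20 equal sites. The design effect applies to the Savi Scout group only, since the wire cohort comes from one institution.

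**1. The plan's own figure.** The binomial variance at 0.6% is 0.006 × 0.994 = 0.005964. SE of the difference = √(2 × 0.005964/1000) = 0.003454. Then (1.645 + 0.842) × 0.003454 = 0.859%, which rounds to the stated 0.9%. At a margin of exactly 0.9%, power is Φ(0.009/0.003454 − 1.645) = 83%. The statement in 8.1 therefore reproduces, under independence.

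**2. Effect of clustering on the comparison.** Design effect DE = 1 + 49 × ICC.

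- Effective n = 1000/DE.
- Power = Φ(0.009/√(0.005964 × (DE + 1)/1000) − 1.645).
- One-sided error, taken at the margin (1.5% against 0.6%): the variance at 1.5% is 0.015 × 0.985 = 0.014775. SE_naive = √((0.014775 + 0.005964)/1000) = 0.004554 and SE_true = √((0.014775 × DE + 0.005964)/1000). Error = 1 − Φ(1.645 × SE_naive/SE_true).

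| ICC | DE | Effective n | One-sided error | Power |
|---|---|---|---|---|
| 0.001 | 1.05 | 953 | 5.3% | 82% |
| 0.005 | 1.25 | 803 | 6.5% | 79% |
| 0.01 | 1.49 | 671 | 7.8% | 75% |
| 0.02 | 1.98 | 505 | 10.3% | 69% |
| 0.05 | 3.45 | 290 | 16.0% | 54% |

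Replacing 49 by 19 or 99 shows the dependence on site size. At ICC 0.01 the error is 6.1% with 20 per site and 10.4% with 100 per site.

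**3. What these ICC values mean.** Between-site SD = √(ICC × p(1 − p)). At p = 0.6%, ICC 0.001, 0.01 and 0.05 correspond to a site SD of 0.4, 1.3 and 2.9 times the mean rate, so the upper values describe very large differences in failure. For re-excision at 12.8%, an assumed site SD of 3 to 5 points gives ICC = 0.03²/(0.128 × 0.872) = 0.008 to 0.05²/(0.128 × 0.872) = 0.022. Values near 0.01 are thus easier to reach for the commoner outcomes.

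**4. Does clustered variance repair it?** I simulated beta-binomial data, 20 sites of 50, 100,000 runs, ICC 0.01, and looked at nominal 95% Wald intervals for one Savi Scout rate (cluster-robust with a t quantile on 19 df).

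| Outcome | Unadjusted coverage | Cluster-robust coverage |
|---|---|---|
| 12.8% re-excision | 89.5% | about 95% |
| 0.6% failure | 88% | 90% |

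For the rare outcome the repair largely fails. Expected failures are 1000 × 0.006 = 6, and even without clustering 20 × 0.994⁵⁰ = 14.8 of the 20 sites have none. At the margin, simulated one-sided error at ICC 0.01 is 10.0% unadjusted and 8.7% cluster-robust (normal quantile). It is already 6.5% at ICC zero, so part of the excess comes from Wald limits on few events and not from clustering.

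**The case against.** The strongest reply is that 8.2 also plans a regression, that this could carry a site term, and that model terms are commonly settled in a statistical analysis plan, which is not shown here. This stands in part: the protocol does not exclude a site term, and it would be wrong to say that it plans only unadjusted tests. But no site term is named, adjusting for covariates does not by itself correct the variance, and the between-group tests that are named rest on independence.

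A second reply is that the size is assumed. That stands. At ICC 0.001 the error is 5.3% and power still exceeds the stated 80%. A reader might infer that the one-sided 5% error is certain to be materially exceeded. The documents do not support this, because they give neither the ICC nor the number of sites.

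A third is that the skew described in 5.5 concerns a dominant contributor, which is a matter of bias. That stands too. A reader might infer that GEE or a random intercept would cure the limitation. It would widen the intervals and leave the bias, because the wire cohort comes from one institution and site is largely confounded with method.

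Finally, a reader might add correlation between several reflectors in one patient. The protocol does not describe bilateral or bracketed placement, and it counts patients (8.1) and participants (4.2). That supports stating the patient as unit, but not a claim that reflectors are being miscounted.

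**Conclusion.** The point holds in a limited form. The named tests assume independence, while 5.5 expects centre differences and 6.1 describes a many-site against one-institution comparison. The direction is clear: with any positive within-site correlation, unadjusted standard errors and p-values for pooled Savi Scout outcomes are too small. The size is open. With 50 per site it runs from negligible (5.3% one-sided error, 82% power at ICC 0.001) through moderate (7.8%, 75% at 0.01) to serious (16%, 54% at 0.05). These figures rest on equal site sizes, clustering in the Savi Scout group only, and a normal approximation that is rough for about 6 events.

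The practical consequence is greatest for margin status and reoperation, where clustered variance works. For the failure rate it helps little. The power statement in 8.1 is reproducible as written, and the issue there is only the independence that it takes for granted.

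**What to change.** In section 8.2:

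- State that the patient is the unit of analysis.
- For the commoner outcomes (margin status, reoperation), report Savi Scout rates and intervals with site-clustered variance: GEE or cluster-robust standard errors with a small-sample correction, or a site random intercept.
- For the failure rate, tabulate failures and denominators by site, with a leave-one-site-out check presented as description. Do not rely on cluster-robust Wald limits.

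In section 5.5, keep the present limitation and add that the wire cohort comes from one institution, so that site is confounded with method and clustered variance does not remove the resulting bias.

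The cost is a few sentences and wider intervals, appreciably wider if the ICC is high: at 50 per site the factor on a single-rate interval is √1.49 = 1.22 at ICC 0.01 and √3.45 = 1.86 at 0.05. Section 11 refers to site-specific data, so the contributing centre should be identifiable without further collection.

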**9. DATA COLLECTION AND CONFIDENTIALITY AND STORAGE AND ARCHIVING OF STUDY**

Confidentiality, storage and archiving will be conducted according to Australian and NSW Research Standards.

Each participant will be given a unique study identification code and data will be entered and stored using this code. This will be used to collate their data in a de-identified manner and link this data to their clinical history. Data will be collected on the electronic REDCap system, hosted by Manchester University NHS Foundation Trust/Manchester University. REDCap is a secure, web-based application designed exclusively to support data capture for research studies REDCap provides: 1) an intuitive interface for data entry (with data validation); 2) audit trails for tracking data manipulation and export procedures; 3) automated export procedures for seamless data downloads to common statistical packages (SPSS, SAS, Stata, R); and 4) procedures for importing data from external sources.

REDCap is developed and maintained by a team at the Vanderbilt University and licensed free of charge. Access to a REDCap database is restricted and password protected. Only the study investigators will have access to completed consent data and research data. In this study the REDCap database is designed by Vanderbilt University and hosted by Manchester University NHS Foundation Trust/Manchester University.

For analysis, the deidentified participant data will be exported from REDCap at Manchester University for statistical analysis.

The CPI is the administrator of the account and will be the custodian of the data. Ownership and access will be restricted to active Investigators on the Project. When an Investigator is no longer active their access will be deactivated, and Ethics will be notified. If the CPI is changed then Ethics will be notified.

9.1. FORMS AND PROCEDURE FOR COLLECTING DATA

Data will be collected via the REDCap system and the CRF that is attached identifies the data fields for data collection.

There will be no images collected for this study.

Artificial intelligence will not be used for data collection in the study.

9.2. SYSTEMS

REDCap has been disseminated for local use at more than 1,005 other academic/non-profit consortium partners in 79 countries. Vanderbilt leads the REDCap Consortium, which currently supports more than 99,000 projects and 128,000 users. More information about the consortium and system security can be found at http://www.projectredcap.org/. REDCap is a secure, web-based application designed to support data capture for research studies, providing 1) an intuitive interface for validated data entry; 2) audit trails for tracking data manipulation and export procedures; 3) automated export procedures for seamless data downloads to common statistical packages; and 4) procedures for importing data from external sources.

REDCap is created by Vanderbilt University, with the server hosted by the University of Manchester. REDCap was developed specifically around HIPAA-Security guidelines. Web browser communication to the server is SSL-encrypted by default. All other ports are firewall protected. Data is stored in MySQL databases on a separate server. This server is behind a firewall and can only be accessed from the IP address of the web server. An SSL- tunnel encrypts communication between the web and databases servers. File upload is secured between servers using theWebDAV protocol with SSL. "At rest" encryption is in place on the database server (aes-xts-plain64:sha256 with 512-bit keys). Daily back-ups are made of both servers and stored for two weeks prior to being deleted. Operating security updates are installed automatically. Antivirus software runs to a scheduled protocol on the web server. User passwords are managed directly. Accounts are disabled after 5 failed login attempts. Users are auto logged out after 30 mins of no activity. Users are forced to change password after 90 days. Daily audit tracking of users is in place with removal of unused user accounts. REDCap servers are housed at the University of Manchester and all web-based information transmission is encrypted.

Data collection will occur in accordance with Caldicott II principles. Data for each patient will be anonymised using a unique alphanumeric study identification code. No patient identifiable data will be recorded for the purpose of the audit.

